## Methods

The Table 1 shows the SPIRIT schedule of the present study. All the details related to the tools used for the assessments are presented in Table 2.

**Table 1 pone.0301124.t001:** The recommendation of interventional trials (SPIRIT) schedule of enrolment, interventions, and assessments.

	STUDY PERIOD					
	Enrolment	Allocation	Post-allocation			Close-out
TIMEPOINT	*-S* _ *1* _	0	S_*0*_	SI_*1*_	SI_*2*_	S_*1*_
**ENROLMENT:**						
**Eligibility screen**	X					
**Informed consent**	X					
**Allocation**		X				
**INTERVENTIONS:**						
** *Intervention A/Experimental Arm* **				X	X	
** *Intervention B/Control Arm* **				X		
**ASSESSMENTS:**						
***Feasibility of the intervention and adherence*** *Task completion*, *Perceived complexity of tasks*, *Participation in sessions*				X	X	
***Feasibility of the evaluation*** *Completion rate of online surveys*, *Quality of responses*			X			X
***Fidelity of the intervention*** *Exposure to the intervention*, *Perceived responsiveness of participants*				X	X	
***Academic’s behaviours*** *Number of professional trips by air*, *Percentage of home-work trips made by car or other modes*, *Frequency of purchasing of equipment*, *Use of alternatives to air travel*				X		
***Psychological constructs*** *Intention towards changing behaviours*, *Knowledge about climate change Beliefs about the consequences of behaviour on the climate*, *Self-efficacy*, *Beliefs about negative consequences of reducing air travel*, *Attitude*, *Environmental attitudes*, *Ecological identity*, *habits*, *Compensatory beliefs*, *Self-control resources*, *Descriptive and subjective norms*			X			X
***Sociodemographic and institutional information*** *Gender*, *age*, *number of children*, *self-reported distance between home and work*, *perceived accessibility by train or alternative transport modes*, *income level*, *Career status*, *employer*, *characteristics*, *academic recognition*, *funding for professional mobility*						

Note. S = Session (Survey to be fill up), SI = Session if intervention.

**Table 2 pone.0301124.t002:** Summary of the variables, tools and time measurements.

Outcomes	Tool	S_0_	SI_1_	SI_2_	S_1_
**Main outcomes of the study**					
**Feasibility of the intervention and adherence**					
Task completion	Cheklist of tasks to complete		✔^a^	✔^a^	
Perceived complexity of tasks	Scale of 1 to 3 (easy to difficult)		✔^a^	✔^a^	
Participation in sessions	Rate of participation/absence in sessions		✔^a^	✔^a^	
**Feasibility of the evaluation**					
Completion rate of online surveys	Percentage of completion of online questionnaires	✔^b^			✔^b^
Quality of responses	Duration of each questionnaire (too short or too long times considered low quality)	✔^b^			✔^b^
**Fidelity of the intervention**					
Exposure to the intervention	Duration of each session		✔^a^	✔^a^	
Perceived responsiveness of participants	Scale of 1 to 7 (not at all responsive to very responsive)		✔^a^	✔^a^	
**Secondary outcomes**					
**Academic’s behaviours**					
Number of professional trips by air	Survey	✔			
Percentage of home-work trips made by car et by active and sustainable mobility	Survey	✔			
Frequency of purchasing of equipment	Survey	✔			
Intention towards changing professional trips made by car, reducing home-work trips made by car and frequency of purchasing of equipement	Adapted survey [40]	✔			✔
Use of alternatives to air travel	Survey	✔			
**Psychological constructs**					
Knowledge about climate change	Multiple choice questionnaire	✔			✔
Beliefs about the consequences of behaviour on the climate	Adapted survey [9]	✔			✔
Self-efficacy of choosing an alternative to air travel	Adapted survey [40]	✔			✔
Self-efficacy of choosing an alternative to car travel	Adapted survey [40]	✔			✔
Self-efficacy of making sustainable purchases	Adapted survey [40]	✔			✔
Beliefs about negative consequences of reducing air travel	Adapted survey [20]	✔			✔
Attitudes towards alternatives to air travel	Adapted survey [40]	✔			✔
Attitudes towards alternatives to car travel	Adapted survey [40]	✔			✔
Environmental attitudes	Environmental attitudes scale [41]	✔			✔
Ecological identity	Green identity scale [42]	✔			
Business travel habits by air	Adapted habits scale [43]	✔			
Commuting habits by car	Adapted habits scale [43]	✔			
Compensatory beliefs	Survey [9]	✔			✔
Self-control resources	Subjective vitality scale [44]	✔			✔
Descriptive and subjective norms	Adapted survey [40]	✔			✔
**Sociodemographic and institutional information**					
Socio-demographic questionnaire (Gender, age, number of children, self-reported distance between home and work, perceived accessibility by train or alternative transport modes, income level)	Survey	✔			
Socio-demographic follow-up questionnaire (number of children, self-reported distance between home and work, perceived accessibility by train or alternative transport modes, income level)	Survey				✔
Employment questionnaire (Career status, employer characteristics, academic recognition, funding for professional mobility)	Survey	✔			
Employment follow-up questionnaire (career status, employer characteristics, academic recognition, funding for professional mobility)	Survey				✔

**Note.** By default, the outcomes will be measured by using an online survey. S = Session (Survey to be fill up), SI = Session if intervention, R = Recruitment and enrolment periods.

^a^ indicates that the outcome was measured by a questionnaire by paper

^b^ indicates that the outcome was calculated by a member of the research team based on other data.

### Ethics and data protection

The Fig 1 shows the procedure of ethics, data protection, recruitment, inclusion in the study, allocation, study enrolment and beginning of the study. First, the main researchers of this study contacted the Data Protection officer to establish a detailed planned of data collection and data protection. Then, a detailed document containing the data collection, data analysis and data protection were submitted to the Grenoble Alpes Research Ethics Committee (CERGA). Ma Terre-EVAL pilot study received the ethic’s approval in May 2023 (File CERGA-Avis-2023-11). Moreover, each participant will read and sign a detailed informed consent form (cf. S1 and S2 Appendices.) before starting the study only if he/she agrees to participate in the study.

**Fig 1 pone.0301124.g001:**
[figure not shown]
Procedure of the Ma Terre-EVAL pilot study since the ethics and data protection procedures to the study enrolment and beginning of the study.

### Participants

#### Study setting

This study will be restricted to individuals being employed by a French private or public research organisation. In France, 462k (i.e., considering that, in total 649 1000 people work partial or full time for R&D representing 462K full-time works) of people work full time for a French private or public research organisation [45]. According to a recent survey involving more than 6000 people working in public research centres [20], between 25% and 35% of the respondents have travelled by air for professional reasons between 2017 and 2019. The principal motives of professional air mobility were conferences, meetings, workshops and research visits. According to this same survey, 24% of the respondents commute by car to go to work.

#### Eligibility criteria

To take part in Ma Terre-EVAL pilot study, participants will need to meet the following criteria:

Being over 18 years oldBeing employed by a French public or private research organisation.

### Participant timeline

#### Recruitment, allocation, and blinding

The participants will be recruited through announcements by e-mail sent by the study partners (CNRS, IRD, Univ. Grenoble-Alpes) and “snowball”. The study partners (CNRS, IRD, Univ. Grenoble-Alpes) will relay announcements describing the study and the steps to follow to participate.

The people volunteering to participate in Ma Terre-EVAL pilot study will send an email to the field manager who will call them back to explain the study procedure and verify the eligibility criteria.

Participants accepting to participate will be randomly allocated to the experimental or control arm. For this purpose, previously to the enrolment, the scientific team will create a randomisation list by blocks of ten (i.e., in this randomisation list by blocks of ten, here are five possibilities to be in the experimental arm and five possibilities to be in the control arm).

Concerning the blinding, the implementation team (the facilitators in charge of leading the intervention sessions) will not be aware of the arm allocation at the beginning of the study (S_0_), but blinding will be impossible afterward because the facilitators deliver different contents to each arm through online meetings with the participants. The research team might be aware of the group allocation at the moment of analysing the data of the pilot study because of the missing data (because the control arm will have no information about the second intervention meeting). Nevertheless, the lack of blinding will not be a problem, because the objective of this study is not to determine the effects of the intervention but the feasibility and the fidelity of the intervention and the evaluation.

#### Timeline of the study

Participants enrolled in this study will have a first 45-minutes online meeting with a member of the implementation team (“Session 0” or S_0_, see Fig 2). At the beginning of this meeting, the participant will read and electronically sign and send by mail the consent form (cf. S1 and S2 Appendices). Then, he or she will fill in a questionnaire to report on his or her professional mobility, home-to-work mobility and professional electronic purchases, psychological constructs and socio-economic and institutional information (see Table 2 for all the details about the tools and surveys and see S3 and S4 Appendices).

**Fig 2 pone.0301124.g002:**
[figure not shown]
Calendar of Ma Terre-EVAL pilot study and the measurements. S = Session (Survey to be fill up), M = Month, IM1 = Intervention meeting with experimental and control arm. IM2 = Intervention meeting only with experimental arm. Notebook = Online survey.

Approximately two weeks after this session, participants of both experimental and control arm will have the first intervention meeting (IM_1_) with another four participants of their same arm and a facilitator (1 hour). During this meeting, the participants will have a discussion aiming to raise awareness between academic behaviours and environmental issues (all the details of this session will be described in the section “Intervention”). At the end of this meeting, participants of both arms will be asked to evaluate their carbon footprint through the Micmac app (https://avenirclimatique.org/micmac/simulationCarbone.php) and send it to the implementation team.

Approximately two weeks after this first intervention meeting, only the participants of the experimental arm will be contacted to carry out a second intervention meeting (IM_2_) with four participants of their same arm and a facilitator (2 hours and 20 minutes). During this meeting, the participants will participate to the serious game “Ma Terre en 180 minutes” aiming to discuss the possible transition pathways to diminish carbon emissions while playing the role of fictional research laboratory team members (all the details of this session will be described in the section “Experimental Arm”). During and after each of the meetings (IM_1_ and IM_2_) the facilitators will complete a checklist and answer questions about the sessions (see Table 2 and S1–S3 Tables. Tables to be filled up by the facilitators to evaluate de fidelity and feasibility).

Two weeks after the experimental arm’s intervention meeting session (IM2) and one month after the control arm’s intervention meeting session (IM2), the participants will receive a link to complete a 15-minutes online survey (“Session 1” or “S_1_”).

#### Retention of participants

To limit the attrition risk, we will send a newsletter one month after the start of the study to inform about the laboratories involved in the study and a short presentation of the research and field team.

#### Power analysis and sample size

Because our data analysis will be descriptive as a part of the feasibility study, we consider that a power analysis is not necessary [38]. Considering time and resources constraints, we decided to recruit thirty participants (*N* = 30) that will be randomised in the experimental or control arm.

### Intervention

Eligible participants will be randomised in equal proportion to the experimental arm or to the control arm. The intervention for the experimental arm will last for two weeks (including two intervention meetings and a carbon assessment) as the one for the control arm (including only one intervention meeting and a carbon assessment of the one month and a half study period) (Fig 2). The detailed content of the interventions for experimental and control arms will be described in the next subsections (see Table 3 for a summary).

**Table 3 pone.0301124.t003:** Summary of the elements of the experimental and the control arms.

Element	Experimental arm	Control arm
First group appointment with a facilitator	Group discussion about topics related to planetary limits, climate change, distribution of the carbon footprint of some research laboratories and initiatives to decrease the Academia’s carbon footprint.	Group discussion about topics related to planetary limits, climate change, distribution of the carbon footprint of some research laboratories and initiatives to decrease the Academia’s carbon footprint.
Conducting an individual carbon assessment	Online individual carbon assessment related to food, mobility and energy consumption.	Online individual carbon assessment related to food, mobility and energy consumption.
Second group appointment with a facilitator	Group session of the serious game “Ma terre en 180 minutes”. During the serious game, each participant takes on the role of two fictional characters from a research laboratory whose mission is to reduce the laboratory’s carbon footprint by 50%.	

#### Experimental arm

The intervention (Intervention A) to be carried out by this arm consists of an awareness-raising session (one hour in a group of five people with a facilitator), the completion of a carbon footprint assessment and a “Ma Terre en 180 minutes” game session (2 hours 20 minutes in a group of five people with a facilitator).

During the first online 1-hour meeting (Intervention meeting 1, IM_1_), the facilitator and the group of five participants will discuss about the energy consumption and the basic human’s needs, planetary limits, climate issues, current carbon footprint of a random French person and target carbon footprint according to the Paris Agreement, the link between activities in an academic life and carbon footprint, the distribution of the carbon footprint of some laboratories and the initiatives to diminish it. At the end of the meeting, they will collectively make an astonishment report using virtual Post-its. The behavioural change techniques [31] that were targeted by these activities are “5.2 Salience of consequences”, “5.3 Information about social and environmental consequences”, “6.3 Information about others’ approval” and “4.1 Instruction on how to perform the behaviour”.

After the first meeting of the intervention, the study participants are encouraged to carry out an online carbon footprint assessment by using a free tool: https://avenirclimatique.org/micmac/simulationCarbone.php. This takes between ten and fifteen minutes and requires precise information about the household energy consumption. The behavioural change technique [31] that was targeted by this activity is “2.2 Self-monitoring of behaviour”.

During the second online 2 hour and 20 minutes meeting (Intervention meeting 2, IM_2_), the group of five participants play the serious game “Ma terre en 180 minutes” (see Fig 3 to see an example of a game table or http://51.178.55.78/MT180/mt180.htm) under the gaze of the facilitator who answers questions and paces the game steps. During the game session, each player takes on the role of two characters from a research team and begins a free negotiation followed by a guided negotiation aiming at a 50% reduction of the research laboratory carbon footprint. In addition, after the end of the game, the facilitator leads a debriefing session with the participants. The behavioural change techniques [31] that was targeted by the serious game and its debriefing are “6.2 Social comparison”, “5.2 Salience des consequences”, “13.2 Framing/reframing”, “6.1 Demonstration of the behaviour”, “4.1 Instruction about how to perform a behavior”, “12.2 Restructuring the social environment”. Moreover, the detailed content of the intervention is available on S5 and S6 Appendices.

**Fig 3 pone.0301124.g003:**
[figure not shown]
Example of a game board from the serious game “Ma terre en 180 minutes”. The tokens show the different sources of carbon footprint of each fictional character (e.g., travel for conferences or field missions, commuting). The bigger tokens indicate bigger carbon footprints.

#### Control arm

The intervention (Intervention B) to be carried out by this arm consists of an awareness-raising session (one hour in a group of five people with a facilitator) and the completion of a carbon footprint assessment.

During the first online 1-hour meeting (Intervention meeting 1, IM_1_), the facilitator and the group of five participants will discuss about the energy consumption and the basic human’s needs, planetary limits, climate issues, current carbon footprint of a random French person and target carbon footprint according to the Paris Agreement, the link between activities in an academic life and carbon footprint, the distribution of the carbon footprint of some laboratories and the initiatives to diminish it. At the end of the meeting, they will collectively make an astonishment report using virtual Post-its. The behavioural change techniques [31] that were targeted by these activities are “5.2 Salience of consequences”, “5.3 Information about social and environmental consequences”, “6.3 Information about others’ approval” and “4.1 Instruction on how to perform the behaviour”.

After the first meeting of the intervention, the study participants are encouraged to carry out an online carbon footprint assessment by using a free tool: https://avenirclimatique.org/micmac/simulationCarbone.php. This takes between ten and fifteen minutes and requires precise information about the household energy consumption. The behavioural change technique [31] that was targeted by this activity is “2.2 Self-monitoring of behaviour”. The control group does not participate in the serious game “Ma Terre en 180 minutes”.

The Figs 4 and 5 compares the targeted sources of behaviour (i.e., motivation, opportunity or capability according to [31], the intervention functions (i.e., education, persuasion, incentivisation, coercion, training, enablement, modelling, environmental restructuring and restriction according to [31]) and the behaviour change techniques [31] mobilised in the Experimental and Control arms.

**Fig 4 pone.0301124.g004:**
[figure not shown]
Sources of behaviour targeted by the intervention (in the centre of the circle), intervention functions (in the intermediary part) and behaviour change techniques (in the exterior part) used for the experimental arm.

**Fig 5 pone.0301124.g005:**
[figure not shown]
Sources of behaviour targeted by the interventions (in the centre of the circle), intervention functions (in the intermediary part) and behaviour change techniques (in the exterior part) used for the control arm.

#### Adherence

To measure the adherence to each intervention arm, the facilitator will take notes about the duration of each intervention meeting and of every situation that could disrupt the planned elements of the intervention (e.g., participants not sending their carbon footprints, participants lacking an intervention meeting).

### Outcomes and data collection

#### Primary outcomes and data collection methods

The main outcomes of Ma Terre-EVAL pilot will be the feasibility of the intervention, the feasibility of the evaluation of behavioural changes and the fidelity of the intervention.

The intervention’s feasibility will be operationalised in three variables: 1) Task completion (a checklist of all activities that need to be carried out during the intervention sessions), 2) Complexity of the intervention tasks (a scale of 1 to 3, from easy to difficult) and 3) Percentage of participation in the meetings (percentage of people absent or present at the intervention meetings). All of this information will be collected through paper questionnaire.

The feasibility of the evaluation of behavioural change will be operationalised in two variables: 1) Completion rate of the online questionnaires (average of the completion of each questionnaire) and 2) Quality of the answers (considering the duration of each questionnaire). More precisely, the quality of the answers will allow us to detect participants who potentially do not take the task seriously enough (i.e., with unrealistic short time on certain tasks) by calculating the Median Absolute Deviation [46] to detect outliers on the time spent on the page showing the article and will exclude participants with a Median Absolute Deviation superior to 3. Both of these outcomes will be calculated by the scientific team by downloading the online surveys completed by the participants of the study.

Finally, the fidelity of the intervention will be operationalised in two variables: 1) Exposure to the intervention (average time of each session) and, 2) Responsiveness of the participants (via a scale of 1 to 7 from not at all responsive to very responsive, this question will be asked to each facilitator). All of this information will be collected through paper forms. All the details of the variables, tools and measurement times can be found in Table 2.

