#### Statistical methods

*Analysis of the feasibility of the intervention and adherence*. Concerning the Task completion, we will identify the tasks that were not completed (i.e., for each group of participants and for each meeting) and we will calculate the percentage of completion of each task (e.g., the discussion about planetary limits was completed in 100% of IM_1_ for experimental and control arms). Concerning the perceived complexity of tasks, we will calculate the average complexity of each task (from 1 to 3) and look at all the comments noted by the facilitators. Concerning the adherence, a participation/absence rate will be done per each intervention meeting.

*Analysis of the feasibility of evaluation*. Concerning the Completion rate of online surveys, we will calculate the percentage of completion of online questionnaires during the first session of measurement (S_0_) and the second session of measurement (S_1_). Concerning the quality of the responses, we will calculate the Median Absolute Deviation [46] to detect outliers that spent too few or too much time to complete the surveys (participants with a Median Absolute Deviation > 3).

*Analysis of the fidelity of the intervention*. Concerning the exposure to the intervention, we will calculate the average duration of each intervention meeting. Concerning the perceived responsiveness of participants, we will calculate the average of perceived responsiveness per each intervention meeting.

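### The response-quality rule times an article page that no described task contains, conflicts with its other statements on direction and action, and may miss fast responders if run on raw times

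*Protocol article*

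**What the plan says.** Response quality is one of two variables that define the feasibility of the evaluation, itself a main outcome of the pilot. It is described in three places.

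- **Primary outcomes and data collection methods.** The variable is introduced as "Quality of the answers (considering the duration of each questionnaire"). Its purpose is to find people who do not take the task seriously, explained as those "with unrealistic short time on certain tasks". The rule is then set to "detect outliers on the time spent on the page showing the article and will exclude participants with a Median Absolute Deviation superior to 3".
- **Table 2, Feasibility of the evaluation.** The tool is "Duration of each questionnaire (too short or too long times considered low quality").
- **Statistical methods, feasibility of evaluation.** The MAD is used "to detect outliers that spent too few or too much time to complete the surveys (participants with a Median Absolute Deviation > 3"). Exclusion is not mentioned.

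None of these says whether time is analysed raw or transformed, or whether the MAD carries the usual normal-consistency factor.

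**The concern.** The sentence that states the rule most fully names a timed object that does not fit the study. The participant tasks described are the S0 and S1 surveys, the group discussion, the online carbon assessment and, in one arm, the serious game. None involves reading an article.

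The statements also disagree on two choices that change the reported result: whether slow responders count as poor quality, and whether flagged people are removed or only counted. With 30 participants, each removal is 1/30 = 3.3% of the sample.

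A further, conditional worry is the cut-off itself. Completion times cannot fall below zero and often have a long right tail. A symmetric limit on raw minutes can then sit at or below zero on the short side, where careless responding would show. The pilot is meant to tell the team whether its online surveys yield usable answers for the planned large trial, so a rule that misses fast responders could give false reassurance.

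**Working it through.** **Step 1: the statements side by side.**

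| Place | What is timed | Direction | Action |
|---|---|---|---|
| Outcomes section, definition | each questionnaire | not stated | not stated |
| Outcomes section, rule | article page | short (as explained) | exclude |
| Table 2 | each questionnaire | short or long | counted as low quality |
| Statistical methods | the surveys | short or long | detect |

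The article page stands alone against three statements. The direction differs between the outcomes section and the other two places, and exclusion appears once only.

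**Step 2: where the limits fall on raw time.** The plan gives no figure to reproduce. I read a MAD above 3 as a distance from the median of more than 3 MADs.

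From the protocol: cut-off 3; N = 30 (Power analysis and sample size); S1 planned at 15 minutes (Timeline of the study), taken as the median. Assumed: lognormal times with log-SD s, since the documents give no spread; scaling constant c = 1.4826 (scaled) or 1 (unscaled), since none is stated.

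With the median set to 1, the MAD m solves Φ(ln(1+m)/s) − Φ(ln(1−m)/s) = 0.5. The limits are 15 × (1 ± 3cm) minutes.

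| s | m | Scaled limits (min) | Unscaled limits (min) |
|---|---|---|---|
| 0.2 | 0.134 | 6.1 to 24.0 | 9.0 to 21.0 |
| 0.3 | 0.200 | 1.7 to 28.4 | 6.0 to 24.0 |
| 0.4 | 0.264 | −2.6 to 32.6 | 3.1 to 26.9 |
| 0.5 | 0.327 | −6.8 to 36.8 | 0.3 to 29.7 |

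The lower limit is zero when m = 1/(3c). That is 0.225 scaled (s about 0.34, coefficient of variation about 0.35) or 0.333 unscaled (s about 0.51, coefficient of variation about 0.55).

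**Step 3: detection in a sample of 30.** The simulation used 27 lognormal responders plus 3 speeders drawn uniformly between 20% and 30% of the median. It was repeated with several run counts and the results agreed to within about two percentage points. Each cell gives scaled / unscaled.

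| s | Speeders found, raw | Speeders found, log | Others flagged, raw | Others flagged, log |
|---|---|---|---|---|
| 0.2 | 70% / 99% | 100% / 100% | 1.1% / 4.9% | 0.4% / 3.5% |
| 0.3 | 10% / 68% | 91% / 100% | 1.8% / 6.0% | 0.4% / 3.5% |
| 0.4 | 1% / 20% | 51% / 96% | 2.7% / 7.3% | 0.4% / 3.5% |
| 0.5 | 0.1% / 4% | 19% / 75% | 3.8% / 8.8% | 0.4% / 3.5% |

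At each spread tried, log time found at least as many speeders and flagged fewer others. The unstated constant matters by itself: at s = 0.3 it moves raw-time detection between 10% and 68%.

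**The case against.** Four points can be made for the plan.

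- **The rule can be run.** A reader might infer from the article phrase that it cannot. Three other statements point to questionnaire or survey time, so a sensible analyst would use that. The questionnaires are in appendices not shown here, so the absence of an article page is established only for the tasks the article describes. This stands: the phrase is an error to remove, and does not disable the outcome.
- **The weakness on the short side depends on spread.** A reader might infer that the rule will report almost no careless responding whatever happens. The documents do not support that. They do not say raw time, they cite a reference for the method, and they give no spread. With tight times the raw rule works. S0 is completed in a 45-minute meeting with a team member, where times may be tighter than for the unsupervised S1. This also stands.
- **Flagging slow responders is intended.** Table 2 and the Statistical methods both treat too-long times as poor quality, so a slow flag is not in itself a mistake. What remains is the conflict with the outcomes section, which explains the rule by short times alone.
- **Exclusion need not erase the result.** A reader might infer that dropping flagged people removes the very thing being measured. The text does not say they leave the quality count. It could mean detect, count, then drop from other summaries. The gap is that it does not say which analyses lose them.

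**Conclusion.** The textual point holds without any assumption. One primary variable's rule is tied to a timed object that matches no described task, and the protocol disagrees with itself on direction and on whether flagged participants are excluded.

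The statistical point holds conditionally. If the rule is run on raw times and those times are widely spread, it may miss fast responders: detection in the simulation falls from 70% (scaled) or 99% (unscaled) at log-SD 0.2 to 0.1% or 4% at log-SD 0.5. This rests on lognormal times, the assumed spreads and the assumed speeders, none of which the documents supply.

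Severity is moderate. Response quality is one of seven primary variables in a descriptive pilot with no hypothesis tests. The wording should be corrected, but the pilot's other results do not turn on it unless the exclusion is applied to them.

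**What to change.** In both the outcomes section and the Statistical methods:

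- Delete the reference to an article page. Use total completion time per survey, with S0 and S1 handled separately.
- Apply the 3-MAD rule to log time: flag when |log time − median of log time| exceeds 3 × c × MAD of log time, and state c.
- State that both directions count, and report the numbers flagged fast and slow, by arm.
- State that flagged participants stay in the feasibility and completion outcomes. If they are to be left out of any other summary, name it.

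Optionally, add a pre-set minimum plausible time, because detection on log time also falls when spread is wide (19% scaled at log-SD 0.5). The investigators should choose and justify its value; the documents offer no basis for one.

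The cost is a few lines of text, since the durations are already to be collected. The small downside is that slightly fewer slow responders will be flagged than on raw time.
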